The effect of the PD intervention will be considered in two ways. Firstly, we will compare 45 intervention and 45 control centres for environmental quality in order to estimate the effect upon staff behaviour in the centres. ECEC room-level outcomes will be analysed using linear regression models with post-test outcomes as dependent variables and baseline measures as independent variables. Child-level data analyses will control for clustering within centres using multilevel models (hierarchical models or random-effect models), which can account for clustering of repeated assessments within individuals and clustering of individuals within centres. Post-test scores for primary and secondary outcomes will be used as dependent variables, with baselines variables and group membership as independent variables. Multiple imputation methods will be used for missing individual outcome data. If data are normally distributed we will fit linear models. If not, we will categorise outcome data and use longitudinal logistic regression to evaluate the differences between intervention and control groups. Sensitivity analyses will be conducted for all primary and secondary outcomes. Inverse probability weighting will be considered if missing data are more prevalent than expected and/or there is differential attrition between trial arms. Additionally, reasons for the differential attrition will be fully explored. Secondary analyses from explicit hypotheses (e.g. subgroup, including level of deprivation) will be specified in advance in a statistical analysis plan.

In applying power calculations, we took into account that children are clustered in centres.

Conservative power estimates, after adjusting for the clustered (nested) design, indicate that we can detect an effect size as low as 0.17 standard deviation (SD) units with 80% power for all child outcomes. This is based on a conservative estimate of 13 children per centre, yielding an estimated sample size of 1170. For continuous outcomes, these correspond to differences between the means in the treatment and control groups in units of the SD.

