Detectable effect sizes depend on:The type I error rateThe unit of comparison, i.e. children (*N* = 1170) or centre (*N* = 90)For children, whether measures are independent observations or clustered within centresWhere children are assumed to be clustered within centres, how much of the variability is between centres and how much of the variability is between children within centres

For 80% power, this study would be capable of detecting an effect size for the child outcomes of between 0.17 and 0.20 (*p* < .05) or between 0.21 and 0.24 (*p* < .01), depending on the ratio of the SD of children within centres to the SD of centres. This compares with detectable effect sizes of between 0.16 (*p* < .05) and 0.20 (*p* < .01) if the child measures could be assumed to be independent.

Some of the secondary outcomes involve differences between intervention and control groups at the centre level. Contrasting the child-level outcomes, the differences at the ECEC room level would need to be 0.60 SD units for statistical significance. The design is thus less sensitive for detecting room-level differences than for detecting difference at the child level. While sensitivity for detecting room-level differences could be improved by increasing the sample of centres, the cost implications made this impractical.

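### A normality check decides whether child outcomes, including both primary language scores, are categorised and moved to logistic regression, off the only scale on which power is stated

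*Protocol article*

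**What the plan says.** All of this is in the protocol article under Statistical analyses and power. The child-level model is set out first: "Post-test scores for primary and secondary outcomes will be used as dependent variables, with baselines variables and group membership as independent variables". The form of the model is then made conditional on the data: "If data are normally distributed we will fit linear models". The alternative follows at once: "If not, we will categorise outcome data and use longitudinal logistic regression to evaluate the differences between intervention and control groups". Nothing exempts the two primary outcomes (verbal comprehension and expressive vocabulary), and the wording is a commitment rather than an option to be considered.

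The power statement in the same section claims that "we can detect an effect size as low as 0.17 standard deviation (SD) units with 80% power for all child outcomes". Its basis is described as follows: "This is based on a conservative estimate of 13 children per centre, yielding an estimated sample size of 1170". The scale is a difference in means: "For continuous outcomes, these correspond to differences between the means in the treatment and control groups in units of the SD". No power is given for an odds ratio. The number of categories and the position of the cuts are not stated.

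**The concern.** There are three problems with the rule as stated.

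- **The trigger tests the wrong thing.** It looks at the distribution of the outcome data. A linear model makes no assumption about raw scores. Its assumption concerns residuals, and in a trial of this size even that matters little for comparing means.
- **The effect measure follows the data.** A mean difference becomes an odds ratio at a cut-point. If one language score passes the check and the other fails, the two primary results cannot be set side by side, and one of them is on a scale for which no power is claimed.
- **Categorising usually costs precision.** All children on one side of a cut are treated as alike, although the instruments yield graded scores.

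At stake are the interpretation of the primary comparison and, depending on how the categories are formed, part of the sensitivity for which the trial was sized.

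**Working it through.** **Inputs from the protocol.** 90 centres, 45 per arm; 13 children per centre; N = 1170; 80% power; alpha 0.05 and 0.01. **Assumptions.** Two-sided tests. The intra-class correlation (ICC) is not stated, so it is solved for below. The baseline correlation r is not stated; 0.7 is used for illustration.

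**1. Reproducing the stated detectable effects.** For independent children the detectable effect is 2(z_alpha/2 + z_0.80)/√N.
- Alpha 0.05: 2(1.960 + 0.842)/√1170 = 0.164 (stated 0.16).
- Alpha 0.01: 0.200 (stated 0.20).
- With clustering, multiply by √(1 + 12·ICC). The stated 0.17 to 0.20 at alpha 0.05 implies an ICC of about 0.006 to 0.041. That range gives 0.207 to 0.244 at alpha 0.01 (stated 0.21 to 0.24).

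The stated figures reproduce as a comparison of means with no baseline covariate.

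**2. Information kept when a normal score is categorised.** This is the sum over categories of (difference in normal density between the two cut-points)² / (category probability). For one cut at proportion p it reduces to φ(z_p)²/[p(1 − p)]. Power is Φ(√E × 2.802 − 1.960), where E is the fraction kept; the detectable effect is divided by √E.

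| Categories | Kept | Lost | Power (from 80%) | Detectable effect (from 0.17-0.20 SD) |
|---|---|---|---|---|
| Median split | 0.637 | 36% | 61% | 0.21-0.25 |
| Split at 25/75 | 0.539 | 46% | 54% | 0.23-0.27 |
| Split at 20/80 | 0.490 | 51% | 50% | 0.24-0.29 |
| Tertiles | 0.793 | 21% | 70% | 0.19-0.23 |
| Quartiles | 0.861 | 14% | 74% | 0.18-0.22 |
| Quintiles | 0.897 | 10% | 76% | 0.18-0.21 |

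For the median split, 1170 × 0.637 ≈ 745 effective children, and 1170/0.637 ≈ 1840 would be needed to restore 80%.

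**3. Simulation without a baseline covariate** (90 centres × 13 children, cluster-robust standard errors). At ICC 0.006 and an effect of 0.17 SD, power was 79% for the linear model and 61% for the median split. At ICC 0.04 and 0.20 SD it was 80% and 65%. Further runs put the median split at up to 67%.

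**4. With the planned baseline adjustment, r = 0.7 assumed.** The fraction lost at the median was 43-49% (ICC 0.006 to 0.02), more than without the covariate. Both models gain power, however. At the stated effects the linear model reaches 93-98% and the median split 76-85%. The spread depends on the ICC and on whether baseline also explains differences between centres. The linear end points can be checked by hand:
- ICC 0.04, centre variance unexplained: SE = √[4(0.04/90 + 0.47/1170)] = 0.058, so 0.20/0.058 = 3.44 and power is 93%.
- ICC 0.04, baseline explaining both levels alike: SE = √[0.51 × 4 × 1.48/1170] = 0.051, so 0.20/0.051 = 3.94 and power is 98%.

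**5. Non-normal shapes**, which are the ones that would set off the rule. For a shift in mean, the efficiency of a single cut at quantile q is f(q)²·Var/[p(1 − p)].
- Ceiling-type beta(5,2): 45% lost at the median, 22% or 64% at the quartiles.
- Gamma(2): 22% lost at the median; at the quartiles, from a gain to 65% lost.
- t with 5 df: 4% lost at the median.
- Laplace: a gain at the median.

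**6. Is the switch needed?** With an exponential-shaped outcome and no true effect, a linear test on centre means rejected in 5.0% of 6000 simulated trials.

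**The case against.** The strongest reply is that the default is already the linear multilevel model, and the fallback is conditional and may never reach a primary outcome. Nothing in the protocol suggests that either language test is non-normal, no inflation of type I error is shown, and sensitivity analyses are promised for all outcomes. These are fair limits on the weight of the point. They do not rescue the rule: the sensitivity analyses are unspecified, and they would not restore a primary analysis already moved to a categorised score.

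Four stronger readings are tempting, and the protocol does not support them.

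- A reader might infer that a third or more of the information is always lost. That holds for a two-category split of a roughly normal score. The protocol does not say two categories, and the rule fires on scores that are not normal.
- A reader might infer that power would fall well below the stated 80%. The stated figure carries no baseline covariate, whereas the planned model has one. At r = 0.7 a median split comes out close to 80% (76-85%). A shortfall depends on the cut and on r.
- A reader might infer that cut-points and the normality criterion will be chosen after outcomes are seen. The protocol is silent on this, and these are details that a statistical analysis plan, not shown here, would normally fix in advance.
- A reader might expect the bounded educator-rated subscales to trip the rule. That is plausible, but the protocol gives no distributional data for them.

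**Conclusion.** The point holds as a badly chosen rule, not as a missing detail. A later analysis plan could add cut-points or a normality criterion, but the switch itself would remain. Two parts stand whatever the number of categories: raw-score normality is not required here, and the switch takes the effect off the only scale on which power is stated, possibly for one primary outcome and not the other.

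The information loss is usual but variable: about 36% for a median split of a roughly normal score, more for off-centre cuts or after baseline adjustment, 10-21% for three to five ordered categories, and none to about two thirds for non-normal shapes. These figures rest on two-sided tests, a back-solved ICC of about 0.006 to 0.041 and, where baseline is used, an assumed correlation of 0.7. They do not establish that power would fall below 80%. They do show that the fallback generally gives up precision that the linear model would keep, while guarding against a problem that is small in this design.

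**What to change.** Delete the normality trigger. State that the baseline-adjusted linear multilevel model on the continuous post-test score is the primary analysis for every continuous child outcome, whatever its distribution, and that the effect is reported as a mean difference in SD units.

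For skew or ceiling effects, specify cluster-robust or cluster-bootstrap standard errors. Name in advance a transformed-score or ordinal model as a sensitivity analysis only.

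The cost is a short change of text and a little extra analysis work. Sample size, data collection and the power statement are unaffected.

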### Child characteristics and recruitment

Early in the year following centre recruitment, and preceding the intervention, children in the year before formal schooling (4–5 years of age) will be recruited from participating centres. This involves disseminating Participant Information Sheets and Consent Forms, via the centre, to parents or legal guardians of suitably aged children. Participating children will be those who meet the age-inclusion criteria, returned a signed Parental Consent Form to participate in the study and themselves provide verbal assent to participate. Ninety centres are expected to yield a sample of approximately 1200 4–5-year-old children on whom child assessments will be conducted. There are no further exclusion criteria for child participation.

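### The 0.17 SD detectable effect, labelled conservative and applied to all child outcomes, is the favourable end of the protocol's own 0.17 to 0.20 range

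*Protocol article*

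**What the plan says.** All the power statements are in the protocol article, *Statistical analyses and power*.

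- The headline is introduced by "Conservative power estimates, after adjusting for the clustered (nested) design, indicate that we can detect" and states that "we can detect an effect size as low as 0.17 standard deviation (SD) units with 80% power for all child outcomes".
- Its basis: "This is based on a conservative estimate of 13 children per centre, yielding an estimated sample size of 1170".
- Shortly afterwards, for the same 80% power: "this study would be capable of detecting an effect size for the child outcomes of between 0.17 and 0.20" at p < .05, with 0.21 to 0.24 at p < .01. Where a result falls in the range is said to vary, "depending on the ratio of the SD of children within centres to the SD of centres".
- For comparison, the section gives "detectable effect sizes of between 0.16 (*p* < .05) and 0.20 (*p* < .01) if the child measures could be assumed to be independent".

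Under *Child characteristics and recruitment*: "Ninety centres are expected to yield a sample of approximately 1200" children. The analysis text plans multiple imputation for missing outcomes, and considers inverse probability weighting if missing data exceed expectation or attrition differs between arms. It also specifies models of the post-test score with baseline variables as covariates.

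**The concern.** Two statements in one section describe the same design at the same power and error rate, and they do not agree. One gives a single value, calls the estimate conservative and applies it to every child outcome. The other gives a range whose lower, most favourable limit is that value, and says the position in the range depends on between-centre variation. A figure that is right only at the low-clustering limit is not conservative. Nor can it be asserted for all outcomes when the section itself makes it depend on a variance ratio that can differ between outcomes.

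The headline is the number most likely to be carried into later reports as the sensitivity of the trial. If clustering sits at the other end of the protocol's range, the 80% attached to 0.17 SD is overstated on the basis used to calculate it.

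**Working it through.** **Inputs from the protocol article.** N = 1170 (90 centres × 13 children), 45 centres per arm, power 80%, p < .05 and p < .01. No ICC is given, so it is solved for. Sidedness is not stated; two-sided is assumed and then checked.

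**Formula.** Detectable effect in SD units = (z for alpha + z for power) × 2 × √(DE / N), with design effect DE = 1 + (13 − 1) × ICC.

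**Step 1: reproduce the no-clustering figures (DE = 1).**
- p < .05: (1.960 + 0.842) × 2 / √1170 = 0.164. The protocol gives 0.16.
- p < .01: (2.576 + 0.842) × 2 / √1170 = 0.200. The protocol gives 0.20.
- One-sided tests would give 0.145 and 0.185, which do not match.

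The protocol's figures are therefore two-sided and include no gain from baseline covariates.

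**Step 2: solve for the ICC behind each end of the range.** DE = (stated effect / no-clustering effect)², and ICC = (DE − 1) / 12.

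| Stated effect | DE | ICC | ICC band from rounding |
|---|---|---|---|
| 0.17 (p < .05) | (0.17/0.1638)² = 1.077 | 0.0064 | 0.001 to 0.012 |
| 0.20 (p < .05) | (0.20/0.1638)² = 1.491 | 0.041 | 0.035 to 0.047 |
| 0.21 (p < .01) | (0.21/0.1998)² = 1.104 | 0.009 | 0.004 to 0.013 |
| 0.24 (p < .01) | (0.24/0.1998)² = 1.443 | 0.037 | 0.032 to 0.042 |

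The two error rates imply overlapping ICCs at each end, so the range is internally consistent. A t reference with 88 degrees of freedom gives 0.0045 and 0.038 for the p < .05 ends, which leaves the picture unchanged. As the ratio of within-centre to between-centre SD, √((1 − ICC)/ICC), the two ends are about 12.4 and 4.8.

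**Step 3: power for 0.17 at the other end of the range.** At DE = 1.491 the standard error is 2 × √(1.491/1170) = 0.0714. Then 0.17/0.0714 − 1.960 = 0.42, which gives power of about 66%.

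**Step 4: room for loss.**
- At ICC 0.0064, all 1170 children are needed for 80% power at 0.17. That is 1170/1200 = 97.5% of the children expected.
- Losing 10% of the 1170 at that ICC gives a detectable effect of 0.179 and 76% power for 0.17.
- With no clustering at all, 2 × 544 = 1088 children are needed, so at most 1 − 1088/1170 = 7% of the 1170 could be lost.

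**Step 5: what baseline adjustment would have to deliver.** To bring 0.20 back to 0.17 at ICC 0.041, the variance must fall by 1 − (0.17/0.20)² = 0.28. This assumes the same proportional reduction within and between centres. It corresponds to a baseline to post-test correlation of √0.28 = 0.53.

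**The case against.** **The range is disclosed.** The wording around 0.17 is that of a lower bound, and the 0.20 end appears in the same section with the reason for it. This stands: nothing is concealed, and a careful reader sees both ends. It does not make the favourable end conservative.

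**Conservative may have meant the 13 children per centre.** The word is used there too, but its first use qualifies the power estimates themselves. Nor is 13 clearly cautious, since 1200/90 = 13.3 before any loss. The educator time under *Outcome measures and procedures* (3.3 hours at 10 minutes per child) would imply about 20 children per centre, but that does not fit the explicit expectation of about 1200.

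**The planned analysis adjusts for baseline.** This is the strongest objection. A reader might infer from the arithmetic that the trial has 80% power at 0.17 SD only if centres barely differ and almost no child is lost. The document does not support that. If the baseline to post-test correlation were 0.7 at both levels (an assumption), effects would shrink by √(1 − 0.49) = 0.71, and 0.20 would become about 0.14. Actual sensitivity may therefore be better than any printed figure. What remains is that the printed figures claim no such gain, so it cannot justify the label as written.

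**Stronger figures rest on assumptions.** A reader might also argue that the deliberate spread of centres, or educators rating the SDQ and CSBQ, pushes the ICC to 0.10 or 0.15. Unadjusted power for 0.17 would then be about 50% or 41%. The document gives no ICC, so those values are illustrations, not findings. An attrition rate and separate power figures for the educator-rated scales are details that an article may leave to the statistical analysis plan.

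**Conclusion.** The point holds as a misstatement of a power figure. The protocol labels as conservative, and as valid for all child outcomes, a value that its own range shows to be the most favourable. On the basis that reproduces the protocol's numbers (two-sided, equal clusters of 13, no covariate gain), 0.17 SD at 80% power needs an ICC of about 0.006 and all 1170 children analysed. At the protocol's own 0.20 end (ICC about 0.04), power for 0.17 is about 66%. That figure needs no ICC from outside the document.

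This does not show that the trial is underpowered. The baseline-adjusted model could restore 0.17, and how far depends on a correlation that the document does not state.

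**What to change.** In *Statistical analyses and power*:

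1. Make 0.20 SD the conservative headline at 80% power and p < .05, or quote 0.17 to 0.20 there.
2. Remove the conservative label and the all-child-outcomes claim from the 0.17 figure.
3. State the ICC range behind the two ends (about 0.006 to 0.04 on the present basis, to be confirmed by the sponsor) and the number of children assumed to be analysed.
4. If 0.17 is to be kept because the analysis adjusts for baseline scores, say so and give the baseline to post-test correlation relied on. An R-squared of about 0.28 would be needed at ICC 0.041.
5. Show any attrition-adjusted figure only as a labelled assumption. For example, 15% loss from 1200 leaves 1020 children, 11.33 per centre. At ICC 0.041, DE = 1 + 10.33 × 0.041 = 1.42, and the detectable effect is 2.802 × 2 × √(1.42/1020) = 0.21.

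The cost is a few reworded sentences and a slightly less favourable headline. The number of centres and children, the analysis and the error rate stay as they are.

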### Ethical and research governance approval

The study was granted ethical approval by the University of Wollongong Human Research Ethics Committee Social Sciences (HE15/309) on 8 September 2015. Written consent will be obtained from centre directors (for participation and centre observations), educators (who will complete educator-report measures), and children’s parent(s) or legal guardian(s) as a condition for participation. This will include consent for publication of the study results in anonymised aggregate format. As per Consolidated Standards of Reporting Trials (CONSORT) guidelines, the study’s final reporting will follow the CONSORT Statement and its relevant extensions (e.g. cluster trials, nonpharmacological interventions).

### Study timeline

Recruitment of centres commenced in September 2015 and recruitment of children began in February 2016. Figure 1 provides details of the stages of the study. The trial is set to finish in December 2016.

## Discussion

The study is dependent upon the cooperation of the centres recruited to the study, the staff within those centres and the parents of the children in those centres. Hence, substantial efforts have been expended in producing information leaflets for all concerned to explain the study, its aims and the potential benefits of the study for ECEC centres in the future and the children who will use them. A substantial amount of time has been required for meetings and other liaison between the research team and potential centres for recruitment. Thus far, we believe that the necessary groundwork has been made and hope that the study will proceed according to plan. This would mean that the next publication regarding this trial will concern its results, indicating whether there is an impact of the PD programme on child outcomes as a consequence of improved centre staff practice and pedagogy.

While the FEEL study was designed to yield the strongest possible evidence of intervention efficacy, the study is limited in its focus on intervention evaluation and does not, at present, include further qualitative evaluation (e.g. case studies of centres with the greatest and least change, process evaluation, analysis of PD participants’ feedback and comments). This is due to constraints of the available funding, but could be added should funding become available for these important follow-on investigations. Even in lieu of these additions, the results of the FEEL study should inform decision-making about future practice and policy regarding the provision of evidence-based PD to ECEC staff, as well as potentially informing the content of staff training. Such an impact would be of benefit to ECEC centres and their staff, as well as the communities, families and children who utilise these centres.

